### Sensitivity analyses and modification of treatment effect

Although randomisation is designed such that, on average, treatment groups will be balanced with respect to all baseline prognostic factors, this may not be true in all cases. As a result, we will re-assess treatment effects as observed in the original analysis after adjusting for factors that are potentially imbalanced across randomised arms. If imbalance occurs, we will compare and present the results for both unadjusted and adjusted analyses.

In addition, the study was not designed to detect effect modification of the treatment effect among subgroups of children. As a result, we acknowledge that we are likely underpowered to detect differences in the magnitude of a treatment effect among subgroups unless there is strong effect modification. The potential baseline effect modifiers we plan to explore include: study site (India/Tanzania), child age (<12 vs >12 months), child sex (male vs female), prior receipt of rotavirus vaccine (yes vs no), maternal HIV status (yes vs no), dysentery at enrolment (yes vs no), baseline dehydration status (yes vs no), baseline axillary temperature (<38°C vs >38°C), baseline respiratory rate, recent antibiotic use (yes vs no), intercurrent illness (cough, difficulty breathing or earache), current breastfeeding status (yes vs no) and prior breastfeeding status (yes vs no). Additional variables that we will test for effect modification will include child anthropometric measures (length/height for age, weight for age and weight for length/height z-scores and MUAC), family socioeconomic status (<median wealth index, >median wealth index), maternal education, household water quality (improved vs unimproved), household sanitation quality (improved vs unimproved), baseline plasma zinc levels (<median, >median) and trial regimen adherence (<median, >median). Factor analysis will be used to derive wealth index from family possession variables. WHO/Unicef Joint Monitoring Programme definitions will be used to clarify improved versus unimproved for the household water quality and sanitation.^16^

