### Randomisation, allocation, concealment and masking

Trial arm allocation was performed according to a computer-generated randomisation list (generated off-site by a non-study statistician) of 4500 individuals, stratified by country and child age (>6 to <24 months vs >24 to <60 months). A statistician will hold the randomisation list codes until completion of primary analyses or until requested by the Data and Safety Monitoring Board (DSMB). Within each stratum, subjects are randomly assigned equally in permuted blocks of variable size to receive one of the three doses of zinc. The purpose of the stratification is to have equal distribution of younger and older children among all three treatment groups. An independent pharmacy team prepared the zinc regimen in Geneva by labelling blister packs with participant IDs based on the randomisation list. Labels were printed at WHO, Geneva and enrolled children were assigned sequential serial numbers. These prelabelled regimens were shipped to the sites in Tanzania and India. The packing and physical appearance of the three study regimes are identical. In addition, the three doses of the regimen are similar in taste, appearance and smell. As a result, the research teams, study staff as well as caregivers are fully blinded to treatment arm. Zinc formulations are serially numbered according to the randomisation codes. The code is kept in a password-protected spreadsheet file by WHO personnel and is not available to the investigators until the end of the study. This randomisation list was converted into unique sequential serial numbers for each enrolled child at each site. This code will only be broken if the DSMB requests this information for a participant (should they suspect a relationship of a suspected severe adverse event [SAE] to the study drug) or for a study arm (in their interim analyses).

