A baseline assessment, including a detailed physical examination (record of vital signs, axillary temperature, respiratory rate, pulse rate, hydration and nutritional status), will be performed by a research physician at the time of screening for enrolment. The child is evaluated for any Integrated Management of Childhood Illness general danger signs (unable/able to drink or breast feed, convulsions, vomiting, unconscious, stiff neck) and evidence of dehydration or pneumonia, as well as information on recent medical history (duration of diarrhoea, bloody stool/dysentery, recent fever). Vital signs (temperature/heart rate/respiratory rate) in dehydrated child are recorded after the child is rehydrated and stabilised and remaining clinical assessment/screening is completed thereafter. Anthropometry measurements will be taken after rehydration and stabilisation as required, before completing the screening for enrolling the participant. Weight will be measured using an electronic scale with a sensitivity of ±10 g by two independent observers: length (for children aged <24 months) or height (for children aged 24 months or older), which will be measured using a length board within 0.1 cm. Mid-upper arm circumference (MUAC) will be measured using non-stretchable tape to the nearest 0.1 cm. All anthropometric measures will be recorded in duplicate (India) and triplicate (Tanzania). Once these measurements and other eligibility criteria are met, the subject will get enrolled.

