### Analysis of primary outcomes

#### Primary outcome 1

Number (%) of subjects with diarrhoea episodes >5 days. The last day of diarrhoea will be defined as the day in which there is passage of the last liquid or semi-liquid stool prior to two diarrhoea-free days (days when less than three loose stools/day). The duration of diarrhoea will be defined as the number of days between randomisation (not the reported day of onset of diarrhoea symptoms before randomisation) and the last day with diarrhoea. Children who are lost to follow-up, die or withdraw before 5 days will be excluded from this analysis. For the primary analysis, we have set the threshold for non-inferiority of lower doses of zinc (10 or 5 mg/day) as compared with the standard 20 mg/day at <4% in absolute risk (risk difference) compared with the standard dose in the proportion of subjects with prolonged diarrhoea. The proportions of participants with a prolonged diarrhoea episode (defined as >5 days) will be calculated in all treatment arms, and the risk differences (and their 95% CIs) between the lower doses (5 and 10 mg/day) and the standard dose (20 mg) will be estimated. A Cochran-Mantel-Haenszel approach will be used to take stratifying randomisation factors, for example, country and age groups, into account. If the upper limit of the 95% CI for the risk difference is <4%, we will conclude non-inferiority for one or both lower dose arms. We will also examine the RR of prolonged diarrhoea episodes in both lower dose arms compared with the standard dose arm using RR regression which accounts for factors included in the stratified randomisation. In secondary analyses, Cox proportional hazard models will be used to estimate HRs and their 95% CIs for recovery from diarrhoea in each of the lower dose arms compared with the standard dose arm. The time to recovery is defined as the duration of diarrhoea as noted above.

#### Primary outcome 2

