Total number of loose or watery stools after enrolment. An analysis of covariance (ANCOVA) approach will be used to estimate the mean differences and their 95% CI in the total number of loose or watery stools after enrolment for each lower dose arm compared with the standard dose arm, while accounting for the stratified randomisation design. The non-inferiority margin was set at two stools, therefore if the upper limit of the 95% CI is less than two stools, we will reject the null hypothesis that the lower dose zinc is inferior to the standard dose in terms of reducing the total number of loose or watery stools.

#### Primary outcome 3

Vomiting within 30 min after administration of the trial regimen. We hypothesise that the lower dose of zinc will be associated with a reduced risk of vomiting and therefore a superiority test will be used. Vomiting within 30 min of each daily zinc dose is repeatedly measured during the 14-day administration period. Generalised estimating equations (GEE) with the log link, binomial variance and exchangeable correlation matrix will be used to assess the RR of vomiting among the three treatment arms. The exchangeable working covariance matrix and robust estimators of the variances will be used to construct CIs. The robust estimators are consistent estimators of the variances even if the working correlation matrix is misspecified. Stratified randomisation factors will be considered in the model. A secondary analysis concerning severe vomiting (defined as vomiting requiring hospitalisation or vomiting requiring intravenous fluids) will also be performed in similar fashions. We will also examine the proportion of children ever vomiting between the treatment arms and examine whether the RR of vomiting differs by follow-up day.

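### Outcomes 1 and 2 are adjusted for the randomisation strata only, and other covariates enter only if they look imbalanced; pre-enrolment diarrhoea duration, recorded and probably prognostic, is in no stated model

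*Protocol article*

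**What the plan says.** All references are to the Protocol article.

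- **Strata.** Randomisation is "stratified by country and child age", with age in two groups (Randomisation, allocation, concealment and masking).
- **Outcome 1, diarrhoea >5 days.** "A Cochran-Mantel-Haenszel approach will be used to take stratifying randomisation factors, for example, country and age groups, into account" (Analysis of primary outcomes). Non-inferiority is concluded if the upper limit of the 95% CI for the risk difference is below 4 points.
- **Outcome 2, stool count.** An ANCOVA gives the mean differences "while accounting for the stratified randomisation design". The margin is two stools. No other covariate is named.
- **Outcome 3, vomiting.** For the GEE, "Stratified randomisation factors will be considered in the model".
- **Other covariates.** Under Sensitivity analyses and modification of treatment effect, the plan says "we will re-assess treatment effects as observed in the original analysis after adjusting for factors that are potentially imbalanced across randomised arms" and "If imbalance occurs, we will compare and present the results for both unadjusted and adjusted analyses". It names no factor to adjust for and defines no threshold for imbalance.
- **Time already ill.** Eligibility admits acute diarrhoea of less than 72 hours. Duration of the outcome episode is counted from randomisation, "not the reported day of onset of diarrhoea symptoms before randomisation". The baseline assessment records "recent medical history (duration of diarrhoea, bloody stool/dysentery, recent fever". Pre-enrolment duration is not a stratum, not a named covariate, and not among the listed effect modifiers.

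**The concern.** Two children with the same total episode length can differ by almost three days on the outcome, solely because one was enrolled early and the other late in the illness. Against an assumed mean duration of 3.0 days (SD 2.7, Table 1) and a 5-day cut-off, that is a large potential source of variation. It is measured before treatment and costs nothing to use.

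A covariate earns its place in a model by predicting the outcome. A rule that admits covariates because the arms happen to differ on them can pass over a strong predictor that is balanced and admit a weak one that is not. It also leaves the content of the adjusted analysis open until the arms have been compared. At stake are some precision, mainly for outcome 1, and the standing of the adjusted result if it falls on the other side of the margin from the primary one.

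**Working it through.** **1. Reproduce the stated sample size for outcome 1.** Inputs from Table 1: 16% in both arms, margin 4 points, 90% power, 5% significance, about 5% attrition.

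n = 2 × 0.16 × 0.84 × (z₁₋α + z₀.₉₀)² / 0.04²

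- One-sided 5%: 168 × (1.645 + 1.282)² gives 1439; 1439/0.95 = 1515. The stated 1500 is within 1% of this.
- One-sided 2.5%, which is what the 95% CI rule applies: 168 × (1.960 + 1.282)² gives 1766; 1766/0.95 = 1859.

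So 1500 matches one-sided 5%. The covariate question changes no stated figure.

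**2. Power for outcome 1, unadjusted.** Evaluable per arm: 1500 × 0.95 = 1425. SE = √(2 × 0.16 × 0.84 / 1425) = 0.01373, so margin/SE = 0.04/0.01373 = 2.9125.

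- 95% CI rule: Φ(2.9125 − 1.960) = 83.0%.
- One-sided 5%: Φ(2.9125 − 1.645) = 89.8%.

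**3. Power for outcome 1 with adjustment.** Let R² be the share of outcome variance explained beyond the strata. It is assumed, because the article gives no figure. The SE is multiplied by √(1 − R²).

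| R² | Margin/SE | Power, 95% CI rule | Power, one-sided 5% |
|---|---|---|---|
| 0 | 2.91 | 83.0% | 89.8% |
| 0.05 | 2.99 | 84.8% | 91.0% |
| 0.10 | 3.07 | about 87% | 92.3% |
| 0.20 | 3.26 | about 90% | 94.6% |

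In evaluable children per arm, R² = 0.05 is worth 1425/0.95 − 1425 = 75, and R² = 0.10 is worth 1425/0.90 − 1425 = 158.

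**4. How plausible is each R²?** For a binary outcome at 16%, the predicted risks must have SD √(R² × 0.16 × 0.84).

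- R² = 0.05: 8 points. If half the children sit at each of two values, these are about 8% and 24%.
- R² = 0.10: 12 points, so about 4% and 28%.
- R² = 0.20: 16 points, so about 0% and 32%, which is optimistic for a few baseline variables.

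**5. Outcome 2.** SD 9, margin 2 stools. SE = 9 × √(2/1425) = 0.337. Power = Φ(2/0.337 − 1.960), above 99.9% with or without adjustment. The 95% CI half-width is 1.96 × 0.337 = 0.66 stools unadjusted, and 0.66 × √0.90 = 0.63 at R² = 0.10.

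**6. Error rates.** A normal-theory simulation (400,000 draws, one covariate, R² from 0.05 to 0.20) took imbalance as a baseline difference with |z| > 1.96. One-sided error at nominal 2.5% was:

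- 2.5% unadjusted;
- 2.5% with prespecified adjustment;
- 2.2% to 2.5% when imbalance triggered the adjustment;
- 3.0% to 3.5% only if the more favourable of the unadjusted and adjusted results was taken.

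**The case against.** The strongest reply is that this is a preference about efficiency and not an error. The primary analyses are fixed, randomisation makes them unbiased without the covariate, and step 6 shows their error is correct. **That stands.** A reader might infer bias or inflated error from the omission; nothing in the article supports it.

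The imbalance rule is a sensitivity analysis, announced in advance, with both results to be shown. **That also stands.** A reader might call the adjusted result unplanned, or cite the 3.0–3.5% error. But the adjusted analysis is planned (only its covariates are open), and no text lets the more favourable result decide.

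The magnitudes can be overread in three ways:

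- The 83% starting point comes from sizing at one-sided 5% and deciding on a 95% CI, which is a separate matter. Lack of adjustment did not cause it.
- Table 1's 1460 for stools is close to what a 1-stool margin would give (1388/0.95 = 1462), so a reader might claim a power gain for outcome 2 on that basis. The article states two stools in both places, and at two stools there is no power to gain.
- CMH already uses country and age group, so only variance explained beyond them counts.

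Finally, covariate lists are usual SAP content, and pre-enrolment duration is not barred: it could enter if it looked imbalanced. **This stands in part.** Absence of a list from an article would be no finding. The point is what the article does fix: strata-only accounting in the primary analyses, with observed imbalance as the route in for anything else.

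**Conclusion.** The point holds as an inexpensive improvement and does not correct an invalid analysis. Outcomes 1 and 2 account only for country and age group, and observed imbalance is the stated gateway for other covariates. A recorded baseline variable that the trial's own entry window and clock make likely to be prognostic appears in no stated model. The cost is some precision and a data-driven choice of covariates in the adjusted analysis.

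For outcome 1 a reasonable expectation is 2 to 4 points of power under the 95% CI rule (83% to between 85% and 87%), if R² beyond the strata is 0.05 to 0.10. Reaching 90% would need R² = 0.20. For outcome 2 the gain is a slightly narrower interval. These figures rest on 16% in every arm, 5% loss and an assumed R²; the article gives neither the strength nor the direction of the link between time already ill and the outcome. Vomiting within 30 minutes of a dose is much less affected by this argument.

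**What to change.** Before unblinding:

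- Prespecify one short covariate list for outcomes 1 and 2, used whatever the observed imbalance: the strata plus pre-enrolment diarrhoea duration as recorded (the article gives no unit). Continuous age, and dysentery and dehydration at enrolment, are optional additions.
- For outcome 1, fit a logistic model with this list and report the standardised (marginal) risk difference with a robust SE, so that the 4-point margin keeps its meaning. For outcome 2, put the same list in the ANCOVA.
- Keep the strata-only CMH and ANCOVA results as sensitivity analyses.
- In the section on sensitivity analyses, replace the imbalance trigger with this list.

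The variables are named in the baseline assessment or the effect-modifier list, so no new data are needed. The price is slightly more analysis work and a model-based estimate in place of CMH for outcome 1.

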### Eligibility

Study participants will be eligible for enrolment in the study if they meet the following inclusion criteria: 1) male and female children between 6 and 59 completed months of age, 2) acute diarrhoea duration of <72 hours at the time of screening (defined as three or more loose or watery stools) or dysentery (defined as visible blood in the stool), 3) likely to stay within the study area for the next 2 months and 4) written informed consent is obtained from caretaker.

Children will be excluded if they: (1) have severe acute malnutrition (weight for length/height z-score of <−3 or oedema), (2) have severe dehydration that cannot be corrected within 4–6 hours, (3) have signs of severe pneumonia (characterised by presence of either chest in-drawing and either of the following: convulsions or unconscious or vomiting everything,^13^ sepsis, rapid diagnostic test (RDT)-confirmed malaria or other severe illness, (4) have previously or currently been enrolled in the study, (5) are currently enrolled in another trial, (6) are not intending to remain in study area for the duration of the study, (7) have a caregiver who declines participation in the study, (8) have other child currently enrolled in the study in the same household and (9) have used zinc supplements during the 3 days preceding study enrolment.

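### Four quantitative baseline modifiers are explored only as two groups, which weakens interaction tests that the protocol already calls likely underpowered

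*Protocol article*

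**What the plan says.** Under Sensitivity analyses and modification of treatment effect, four measures that are quantitative at baseline are listed as two-group modifiers:

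- age, as "child age (<12 vs >12 months";
- temperature, as "baseline axillary temperature (<38°C vs >38°C";
- wealth, as "family socioeconomic status (<median wealth index, >median wealth index";
- plasma zinc, in the phrase "baseline plasma zinc levels (<median, >median) and trial regimen adherence (<median, >median".

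The last phrase also splits adherence. Adherence is measured after randomisation, is not a baseline modifier, and is left out of this point.

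Other quantitative measures carry no cut. Respiratory rate stands bare in "baseline respiratory rate, recent antibiotic use (yes vs no", and the anthropometric z-scores and MUAC are named without a split.

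The section presents all this as exploration and warns that "we are likely underpowered to detect differences in the magnitude of a treatment effect among subgroups" unless the modification is strong. Elsewhere, the Randomisation section says that allocation is "stratified by country and child age (>6 to <24 months vs >24 to <60 months". The section on plasma zinc and other secondary outcomes plans restricted cubic splines where the relation with study day is not linear.

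**The concern.** A two-group split treats all children on one side of the cut as alike. If the difference between a lower dose and 20 mg drifts gradually with the modifier, the split ignores the variation within each group, and the interaction test loses power. The protocol already names low power as the weakness of these analyses, so a choice that may lower it further needs a reason, and none is given. The case is clearest for the two median splits: a sample median has no biological or policy meaning, so there is no ground to expect a step there. Age also deserves care, because each arm gives one fixed dose from 6 to 59 months and readers will ask whether the comparison holds across that range. At stake is how informative the exploratory interaction results will be, not the non-inferiority or superiority decisions.

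**Working it through.** **Plan's own figure.** The article states no power or information figure for any interaction, so there is none to reproduce.

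**Inputs from the article.** Cuts at 12 months, 38°C and the median; randomisation strata divided at 24 months; eligible ages "male and female children between 6 and 59 completed months of age".

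**Assumptions, not in the article.** The interaction is linear in the modifier. The distributions of age, temperature, wealth index and plasma zinc are assumed as shown below.

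**Formula.** For a linear interaction, the share of information that a split keeps is the squared correlation, r², between the group indicator and the continuous modifier.

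*Median splits (wealth index, plasma zinc).* For a normal measure, r² = 2/π = 0.637, so 36% is lost. For a right-skewed (lognormal) measure with log-SD 0.25 or 0.5, r² is 0.604 or 0.517, so 40% or 48% is lost.

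*Age.* If ages are uniform over 6 to 60 months, a cut with share c below it keeps 3c(1−c).

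- Cut at 12: c = 6/54 = 0.111, so 3 × 0.111 × 0.889 = 0.296, and 70% is lost.
- Cut at 24: c = 18/54 = 0.333, so 3 × 0.333 × 0.667 = 0.667, and 33% is lost.

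For ages skewed young, a truncated exponential starting at 6 months was simulated:

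| Assumed median age (months) | Share under 12 months | Kept, cut at 12 | Lost, cut at 12 | Kept, cut at 24 |
|---|---|---|---|---|
| 11.5 | 53% | 0.521 | 48% | 0.600 |
| 14.2 | 40% | 0.446 | 55% | 0.689 |
| 17.6 | 30% | 0.397 | 60% | 0.712 |
| 20.2 | 25% | 0.372 | 63% | 0.712 |
| 23.7 | 20% | 0.349 | 65% | 0.705 |
| 33 (uniform) | 11% | 0.296 | 70% | 0.667 |

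*Temperature.* If normal, with 5% to 30% of children above 38°C, r² runs from 0.225 to 0.576, a loss of 78% to 42%.

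**Effect on power.** With two-sided 5% tests, power after splitting = Φ(√r² × (1.960 + z_power) − 1.960).

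- From 80%, r² = 0.637: 0.798 × 2.802 − 1.960 = 0.276, which gives 61%.
- From 80%, r² = 0.521: 0.722 × 2.802 − 1.960 = 0.062, which gives 52%.
- From 80%, r² = 0.296: 0.544 × 2.802 − 1.960 = −0.436, which gives 33%.
- From 50%, where z_power = 0: r² = 0.637 gives 35%, and r² = 0.296 gives 19%.

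**Reverse case.** The squared correlation is symmetric. If the true modification is a step at 12 months and ages are uniform, the split loses nothing and a linear age term keeps only 0.296.

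**The case against.** The strongest reply is that the comparison presupposes its answer. Nothing in the article favours a linear shape over a step, and under a step at the cut the linear term is the weaker test. This stands, and it is why the loss must be stated conditionally and the shape checked with a spline. It has little force for the median splits, where no step has a rationale.

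A second reply is that these analyses are openly exploratory and come with a power warning. That also stands and limits the weight of the point.

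A third is that readers who set policy work in age bands, so estimates on either side of a cut are useful. That is a reason to display them, not to base the test on them.

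Several stronger readings are tempting but unsupported:

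- *All continuous modifiers are split.* Respiratory rate, z-scores and MUAC have no stated cut and may well be meant as continuous.
- *Using 12 rather than 24 months is a contradiction or loses validity.* A modifier need not follow a stratification boundary, and comparisons within any baseline subgroup remain randomised. The choice is only unexplained.
- *Children exactly at a cut are dropped.* The same strict signs appear in the randomisation strata. Read literally, those would leave out 6-month-olds, who are eligible, and every enrolled child must fall in some stratum. This is notation, to be tidied editorially.
- *A null age result would be taken to support one dose for all ages.* The article draws no such inference, and its power caveat warns against it.

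**Conclusion.** The point holds as a modest improvement to exploratory analyses of four measures: age, axillary temperature, wealth index and baseline plasma zinc. If the dose effect changes steadily with the modifier, a median split of a roughly normal measure costs about 36% of the information, and the 12-month age cut costs roughly 48% to 70% over the age distributions tried. The top of the age range needs uniform ages. Temperature could fall outside these ranges, depending on how many children are febrile. If the change is a step at the cut, the loss is zero.

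A reader might infer that the plan throws away up to 70% of its information as a matter of fact, or that the 12-month cut would probably miss a real age effect. The documents support neither. The first depends on an assumed shape and age distribution, the second on an assumed effect size as well. The primary non-inferiority and superiority conclusions do not depend on these tests.

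**What to change.** For age, axillary temperature, wealth index and baseline plasma zinc, base the exploratory arm-by-modifier interaction test on the continuous value: a linear term first, with a restricted cubic spline to check shape, as the plasma zinc analysis already allows for study day. Keep the stated cut-points for displaying subgroup estimates, and add the two randomised age strata (divided at 24 months) to the age display. When editing, write each cut with one inclusive side.

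The cost is a change of wording and a few lines of code, with no new data. There are two small downsides: an interaction slope is less direct to read than two subgroup estimates, which the display addresses, and a spline spends degrees of freedom, so it should serve as the shape check rather than the lead test.
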